### Primary outcome measures

Pain severity, QOL, and physical functioning are key components in a core outcome set for reporting of clinical studies for LBP [36, 37]. Outcome measures will be collected at our biomechanics laboratory during the subjects two baseline visits (week 0) as well as during the two post-intervention visits (weeks 12–13). Table 2 provides the summary of the study outcome measures.

**Table 2 Tab2:** Summary of outcome measures and participant characteristics. Collected weeks 0–1 (baseline) and 12–13 (post-intervention/wait-list controls)

Primary outcome measures	Data collection instrument or method
Back pain severity	11-point Numerical Pain Rating Scale (NRS_pain_)
	Resting and during activity
Pain impact on quality of life (QOL)	Pain medications used
	Medical Outcomes Short Form-36 (SF-36)
	Oswestry Disability Index (ODI)
	Roland Morris Disability Questionnaire (RMDQ)
Gait kinematics and kinetics	3D motion analysis for temporal spatial parameters of gait and trunk away, bilateral (at self-selected velocity, standard velocity)
	Ground reaction forces
Muscle strength	1-repetition maximum (1-RM) on MedX® clinical Machines: abdominal curl, hip adduction, hip abduction, leg press, and lumbar extension
Muscle morphology	Bilateral B-mode ultrasound measures of muscle thickness and cross-sectional area: multifidus, paraspinals, transversus abdominis, and internal oblique
Step count	StepWatch® monitor, 7-day average count
Participant characteristics	Demographics, weight, Body Mass Index, current medical issues, current medications
	Back pain history
	Pain catastrophizing level (Pain Catastrophizing Scale (PCS))
	Kinesiophobia (11-item Tampa Scale of Kinesiophobia (TSK-11))

### Pain severity and pain impact on QOL

The primary outcome will be the change in the 11-point NRS_pain_ score during rest and activity from baseline to 3 months. The scale has anchors of 0 (no pain) to 10 (worst imaginable pain). The NRS_pain_ is an accepted outcome measure as described in the Initiative on Methods, Measurement, and Pain Assessment in Clinical Trials (IMMPACT) [38]. Participants will rate their current, worst, and best NRS_pain_ scores over the last 24 h, and the scores will be averaged to create the resting NRS_pain_ value [39]. The participants will also be asked to rate their pain severity during walking [40]. The number, type, scheduled nature of the medication and the medicine dose used to self-manage LBP symptoms will be self-reported by participants at baseline and weeks 4, 8, and 12.

One general QOL instrument and two disease-specific instruments will be used to determine the impact of LBP on participant perceptions of QOL [37]. General QOL will be measured by the Medical Outcomes Short Form-36 (SF-36), consisting of eight domain scores and two component scores (Mental, Physical). The SF-36 instrument has been used to track QOL after traumatic injury such as amputation [41]. Higher scores reflect higher QOL. Low back pain-specific QOL will be measured using the modified version of the Oswestry Disability Index (ODI) [42] and the Roland Morris Disability Questionnaire (RMDQ) [43]. The ODI contains 10 questions about the patient-perceived impact of pain on personal care, walking, lifting, sitting, standing, sleeping, sex life, social life, and traveling. The RMDQ consists of 24 items relating to difficulties with daily activities, house work, stair climb, walking, speed of movements, standing, appetite, and sleep. Both instruments are valid, reliable, reproducible, and sensitive to treatment interventions [42, 43]. Higher scores for both instruments reflect greater pain impact and disability due to pain.

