**Methods/design:**

This study will be a single-assessor-blinded, pre-post-test randomised controlled trial involving 40 men and women aged 18–60 years with traumatic, unilateral transtibial amputation. Participants will be randomised to a home-based, resistance exercise group (HBRX) or a wait-list control group (CON). The HBRX will consist of 12 weeks of elastic resistance band and bodyweight training to improve core and lumbopelvic strength. Participants will be monitored via Skype or Facetime on a weekly basis. The primary outcome will be pain severity (11-point Numerical Pain Rating Scale; NRS_pain_). Secondary outcomes will include pain impact on quality of life (Medical Outcomes Short Form 36, Oswestry Disability Index and Roland Morris Disability Questionnaire), kinematics and kinetics of walking gait on an instrumented treadmill, muscle morphology (muscle thickness of multifidus, transversus abdominis, internal oblique), maximal muscle strength of key lumbar and core muscles, and daily step count.

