### Study population

A total of 40 transtibial amputees aged between 18 and 65 years will be recruited for this study. Participants will be recruited from a major regional prosthetics center and from the greater north Florida community via relationships with local prosthetic clinics and amputee support groups. Study flyers, social media posts, and online web advertisements will also be used. Participants will be eligible if they meet the following inclusion and exclusion criteria. Inclusion criteria: men or women aged 18–60 years, traumatic transtibial amputation more than 1 year prior to enrollment, current prosthesis worn for at least 6 months, suffering from chronic LBP (>3 months with at least three pain episodes per week), must have regular access to a computer for Skype®, or a mobile phone or iPAD to perform Facetime; prosthesis K-level of K2 or greater (indicating the subject is able to ambulate and traverse low-level environmental barriers such as curbs, stairs, or uneven surfaces) [20]. Exclusion criteria: dysvascular amputation, acute back injury, pregnancy, any other chronic back pathology (i.e., herniated disc, ankylosing spondylosis, other related neurological disease), pain symptoms or functional limitations (including those that may require assistive devices) that preclude participation in resistance exercise or physical activity, back surgery within the past 2 years that restricts daily physical activities, and currently enrolled in any other resistance or strengthening exercise interventions. Written informed consent will be obtained from each participant.

The primary outcome of the study is the Numerical Pain Rating Scale (NRS_pain_) value for LBP. Sample size estimation indicated that a total sample size of 32 was necessary to detect clinically meaningful differences in NRS_pain_ from baseline to week 12. Based on published evidence of comparative studies of resistance exercise and controls on LBP [21], a sample size of 16 per group will yield a power of 80% at an *α* value of 0.05. To account for the anticipated dropout rate of 25%, the enrollment target will be 40.

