### Secondary outcome measures

All of the following secondary outcome measures will be collected the UF Human Dynamics Laboratory in the Orthopaedics and Sports Medicine Institute.

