### Statistical analysis

Statistical analysis will be performed using the Statistical package for the Social Sciences (SPSS v. 24, IBM Corporation, Armonk, NY, USA). An *α* level will be established at 0.05 a priori for all statistical tests. Data will first be examined for normal distribution using the Kolmogorov-Smirnov test, and skewness and kurtosis parameters. Descriptive statistics will be performed to characterize the participants. Means, standard deviation, and frequencies will be obtained for both study groups. The chi-square test for frequency distributions will be used for demographics, and amputation type. Continuous data that are not normally distributed will be transformed prior to analysis.

The main analysis type that will be used to test the hypotheses of aims 1 and 2 will be a mixed-model, repeated measures approach. These analyses will examine the main effects of the exercise treatment on the study outcomes. The independent variables will include study group (HBRX or CON) and time point (baseline, week 12). Dependent variables will include LBP severity, medication use, perceived impact of LBP on QOL (NRS_pain_, medication number, SF-36, ODI, RMDQ) and biomechanical measures (walking velocity, temporal spatial parameters, GRF, key joint angles). Mixed models are the preferred approach to analyze data with repeated measures; these models account for correlation among repeated measurements, flexible time effects, and handle missing data. To test the hypothesis of aim 3, regression analyses will be used to identify significant contributors to the change in pain over 12 weeks. A hierarchical approach will be used to find the model of best fit. Independent variables that will be entered into the models will include changes in lumbar muscle strength, ultrasound measure of lumbar extensor cross-sectional area, and change scores in SF-36, ODI, and RMDQ. In addition to age, sex, and K-classification, models will be adjusted for other participant characteristics if differences are found from baseline to week 12 (Tampa Scale of Kinesiophobia and Pain Catastrophizing Scale scores, daily step number). Subjects who dropped out or missing participant data will not be included in the final analysis, and intention-to-treat will not be utilized. Due to the relatively small study size, actual treatment effects that would be seen may be washed out during an intention-to-treat analysis.

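### The primary outcome is one NRS pain score in some places and two in another, with no success rule, and outcomes called secondary elsewhere sit under a primary heading

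*Protocol article*

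**What the plan says.** **One score.** The abstract (Methods/design) gives pain severity on the 11-point NRS as the primary outcome. Study population, where the sample size is set, says: "The primary outcome of the study is the Numerical Pain Rating Scale (NRS_pain_) value for LBP". Neither place says whether the score is taken at rest or during activity.

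**Two scores.** The endpoint definition in the outcome sections reads differently: "The primary outcome will be the change in the 11-point NRS_pain_ score during rest and activity from baseline to 3 months" (section Pain severity and pain impact on QOL). The same paragraph derives the resting value as the mean of three ratings (now, worst and best) covering the past day. Pain while walking is a further, separate rating. Table 2 also lists both conditions.

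**A wider list under the primary label.** A section and the first column of Table 2 are both headed "Primary outcome measures". In the table, that heading stands over pain, medication, SF-36, ODI, RMDQ, gait, strength, muscle morphology and step count. The abstract differs: "Secondary outcomes will include pain impact on quality of life", and it then adds gait, morphology, strength and steps as secondary. The later section introducing gait, strength, morphology and steps agrees with the abstract: "All of the following secondary outcome measures will be collected". Medication use has no explicit secondary label anywhere.

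**Alpha.** Statistical analysis fixes one rule: the alpha "level will be established at 0.05 a priori for all statistical tests". It gives no order of testing and no adjustment.

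**The concern.** A confirmatory trial needs one stated test, or one stated rule over several tests, on which success is judged. Here the sample size belongs to a single score while the endpoint definition names two. Someone following the text could test the resting score, the walking score, both with either sufficing, or both with each required. These rules have different error rates and different power, and only the first two match the sample size statement. If the choice is made after the data are seen, the nominal 5% no longer describes the chance of a false claim. The primary label over quality-of-life measures blurs the boundary further, because the abstract places them on the other side of it.

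**Working it through.** **Inputs from the Protocol article.** 16 per group, 80% power, alpha 0.05 (Study population); 0.05 for all tests (Statistical analysis); two NRS scores, rest and walking (Pain severity and pain impact on QOL).

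**Assumptions, because the article does not give them.** Two-sided tests, equal true effects on the two scores, and a correlation between the two test statistics anywhere from 0 to 0.9.

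**1. The plan's own figure.** The 16 per group cannot be reproduced, since no effect size or SD is stated. It can be inverted for one outcome:
- Normal approximation: d = (1.960 + 0.842) × √(2/16) = 2.802 × 0.3536 = 0.99.
- Two-sided t-test: d = 1.02.

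So 80% power at 16 per group goes with one score and a standardised difference of about 1.

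**2. One named score at 0.05.** Type I error 5%, power 80%. The stated basis stands.

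**3. Either score suffices, each at 0.05.** If independent, error = 1 − 0.95² = 0.0975. With correlation (simulated pairs of two-sided z-tests, 1,000,000 draws):

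| Correlation | Chance of at least one false positive |
|---|---|
| 0 | 9.75% (exact) |
| 0.5 | 9.0% |
| 0.8 | 7.8% |
| 0.9 | 7.0% |

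**4. Both scores required, each at 0.05.** A false claim on the pair needs a false rejection on at least one score that has no effect, so the error is at most 5%. Power is the chance that both reject when each has 80%:
- correlation 0: 0.80² = 0.64
- correlation 0.5: 0.69 (simulated)
- correlation 0.8: 0.73 (simulated)

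**5. Either suffices, alpha split to 0.025 each.** Error is at most 5%. With d = 1.02 and 16 per group, the t-test power for each score is 0.70. Restoring 80% per score needs 19.5, so 20 per group, or 40 evaluable participants against the planned 32.

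**6. Labels side by side.**

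| Measure | Abstract | Section in the body | Table 2 column heading |
|---|---|---|---|
| SF-36, ODI, RMDQ | secondary | under the primary heading | primary |
| Gait, strength, morphology, steps | secondary | secondary | primary |
| Medication | not listed | under the primary heading | primary |

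The quality-of-life conflict appears in both the section structure and the table. The conflict for gait, strength, morphology and steps comes from the table heading alone.

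**The case against.** A reader might infer that every measure in Table 2 is primary and that success could be declared on any of them, which would push the error rate far above 10%. The article does not support that:
- The same column also holds demographics, back pain history and the two psychological scales, which cannot be outcomes of this kind. The heading is probably a labelling slip.
- Wherever the text defines the primary outcome in a sentence, it is NRS pain.
- Strength, morphology and step count are not among the dependent variables that Statistical analysis lists for aims 1 and 2. Lumbar strength and cross-sectional area enter aim 3 as predictors, and step count as a covariate. An error rate multiplied over the table's rows would count tests that are not planned.
- The Discussion treats improved function or gait without less pain as a separate finding, not as primary success.

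A second tempting inference is that two NRS scores by themselves break the 5% level. They do so only if either suffices. The wording joins rest and activity with an *and*, and no passage states an either-suffices rule.

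It can also be said that an article may leave the handling of two ratings to an analysis plan, and that unadjusted tests of secondary outcomes are common. Both points are fair. They do not remove the conflict: the article itself states the primary outcome as one score where it sizes the trial and as two where it defines the endpoint, and it fixes the alpha rule without linking them.

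**Conclusion.** The point holds in a limited form. The primary outcome is undetermined between one NRS score and two, and the primary and secondary labels conflict, most clearly for quality of life. The consequence depends on the rule eventually applied: error of up to 9.75% if either score suffices; power of about 64–73% if both are required; about 70% per score if alpha is split. The error figures below 9.75% rest on assumed correlations. The power figures rest also on equal effects and on an effect size back-solved from 16 per group, because the article states none. With a single named score, the 5% error rate and the stated sample size basis both stand. No claim is made that the trial's error rate is in fact inflated, only that the text does not exclude it.

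**What to change.** Before analysis:

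1. Name one NRS score at week 12 as the sole primary outcome, tested at 0.05. The resting average is one example; nothing in the article favours it over the walking score, and what matters is that one is fixed. Make the other NRS score the first key secondary, tested only if the primary succeeds. Use the same definition in the abstract, Study population, the outcome section and Statistical analysis.
2. Alternatively, state that both scores must succeed at 0.05, and restate the power or the sample size for that rule.
3. Retitle the outcome section and the first column of Table 2 so that medication, SF-36, ODI, RMDQ, gait, strength, morphology and steps are secondary. Apart from medication, which needs a label of its own, this follows the abstract and the section on secondary outcomes.

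The first option is a change of wording and keeps the stated sample size basis. Its price is that fewer outcomes can carry a confirmatory claim. The second costs power or participants. Trial status reports that recruitment was not complete at submission, so the choice could still be made without knowledge of results if it is recorded before the data are analysed.

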### Secondary outcome measures

All of the following secondary outcome measures will be collected the UF Human Dynamics Laboratory in the Orthopaedics and Sports Medicine Institute.

### Kinematics and kinetics of level gait

To assess the effect of HBRX on gait motion, all participants will undergo a 3D gait analysis at baseline and week 12. Upper and lower body kinematic and kinetic data will be collected using a seven-camera, optical motion capture system (Motion Analysis, Inc., Santa Rosa, CA, USA). The camera capture rate will be 120 Hz. Ground reaction forces (GRF) will be collected at 1200 Hz using a force-plated treadmill (AMTI Inc., Watertown, MA, USA) synchronized to the motion capture system. Thirty-three retro-reflective markers will be used to track movement of the body segments from the shoulder to the foot using the marker method of Kadaba et al. [44]. Kinematic data will be processed using Visual 3D software (C-Motion Inc., Rockville, MD, USA). Kinematic variables (joint segment angular velocity, linear velocity, and joint excursion) will be collected from the frontal, sagittal, and transverse planes for ankle, knee, hip, pelvis, shoulder, and elbow. Gait velocity, cadence, step length, vertical displacement of the center of mass, step width, single and double support times, and lateral trunk sway will be calculated. Lateral trunk sway will be calculated using trunk sway in relation to the pelvis [45]. Peak GRF during gait will be calculated and normalized to body weight [46, 47]. Given that GRF and kinematics are velocity-dependent, walking parameters will be collected at two walking velocities, self-selected comfortable velocity and a standard velocity (1.5 m/s) [48]. Data will be expressed as a percentage of the gait cycle.

### Muscle strength

Lower body muscle strength is expected to change with resistance exercise, and changes in strength can potentially affect outcomes of function and pain [49]. Assessments of strength (one-repetition maximum, 1-RM) will be performed as previously described [54] for abdominal curl, hip adductors, hip abductors, leg press, and lumbar extension using MedX® clinical resistance exercise machines. After a brief warm-up in each machine (completing the motion with minimal resistance), progressively higher loads will be provided until the participant can lift the weight stack only one time with good form. Muscle strength will be defined as the 1-RM value for the exercise. Strength measures will be collected at baseline and week 12.

### Muscle morphology

Morphological changes in lumbar and core skeletal muscle will be assessed using a B-mode ultrasound apparatus (Biosound Esaote MyLab 25) with a linear transducer [50]. Changes in lumbar muscle thickness reflect muscle morphology change due to resistance exercise. The ultrasound technique of Blazevich et al. [51] will capture muscle thickness changes in the paraspinal and multifidus muscles. Once the probe has captured thickness, the probe will be rotated by 90° to capture the cross-sectional view. We can consistently obtain paraspinal and multifidus muscle cross-sectional area values (*r* coefficients in our laboratory = 0.088–0.90 for both muscles). Muscle thickness will be measured as described by Wallwork et al. [52]. The participant will be positioned prone on the clinical table with a pillow under the pelvis to minimize lumbar lordosis for both cross-sectional area and muscle thickness measures. The multifidus muscle thickness will be imaged in the longitudinal view allowing for the visualization of the zygapophyseal joints, multifidus muscle bulk, and thoracolumbar fascia [52]. Thickness will be measured at the levels of L2–3 and L4–5 zygapophyseal joints using on-screen calipers later by a blinded tester. Ultrasound measures of muscle thickness and cross-sectional area from lumbar muscle have very strong intraclass correlations with measures obtained using magnetic resonance imaging (MRI; *r* range 0.919–0.970), and can be a surrogate for MRI [50].

Transversus abdominis and internal oblique muscle thickness changes will be measured from the technique described in Belavý et al. [53]. The participants will lie on their back. The ultrasound probe placement for transversus abdominis and internal oblique will be at the closest point between the iliac crest and the inferior angle of the rib cage. The ultrasound probe will be oriented to initially be perpendicular but then rotated along its axis to visualize the transversus abdominis and internal oblique. One image will capture these muscles. The ultrasound tests will be performed at baseline and week 12.

### Daily step count

Step counts have been previously used to objectively estimate community walking activity in persons with chronic LBP [54]. We will collect the number of steps taken over a 7-day period using an ankle-worn StepWatch® step activity monitor (SAM; Cyma, Seattle, WA, USA). StepWatches® will be worn for a week during baseline testing and post intervention. Steps will be collected and received by the study team at the end of every day over the span of the week. More steps per day is a useful facet of participation in activities that can improve overall QOL [55, 56]. The change in step count from baseline to week 12 will be a covariate used in regression analysis for aim 3.

### Participant characteristics

Age, weight, Body Mass Index, current medical issues, current medications, and back pain history will be collected using electronic case report forms. Kinesiophobia and pain catastrophizing can contribute to physical disability in people with chronic pain [20, 57]. Inclusion of kinesiophobia and pain catastrophizing levels will be necessary for statistical analysis in building the model of best fit in for the third study aim. Both kinesiophobia and pain catastrophizing interfere with engagement in exercise and can decrease QOL in persons suffering from chronic pain. Kinesiophobia and pain catastrophizing levels will be measured at baseline using the modified 11-item Tampa Scale of Kinesiophobia (TSK) [58] and the 13-item Pain Catastrophizing Scale (PCS) [59] as covariates. Other variables that change during the study will also be covariates in the statistical analyses.

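### The rule making variables that change on study into covariates is not confined to aim 3, its change-based trigger is data-driven, and the timing of TSK-11 and PCS is inconsistent

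*Protocol article*

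**What the plan says.** All references are to the protocol article.

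- **Participant characteristics.** Kinesiophobia and catastrophizing are needed "in building the model of best fit in for the third study aim". On timing: "Kinesiophobia and pain catastrophizing levels will be measured at baseline using the modified 11-item Tampa Scale of Kinesiophobia (TSK" and, in the same sentence, the PCS, both as covariates. The paragraph closes: "Other variables that change during the study will also be covariates in the statistical analyses".
- **Daily step count.** "The change in step count from baseline to week 12 will be a covariate used in regression analysis for aim 3". No condition is attached.
- **Statistical analysis, aims 1 and 2.** A repeated-measures mixed model: "The independent variables will include study group (HBRX or CON) and time point (baseline, week 12"). No other term is named, though the verb leaves the list open.
- **Statistical analysis, aim 3.** A hierarchical regression of change in pain: "Independent variables that will be entered into the models will include changes in lumbar muscle strength", with muscle cross-sectional area and changes in SF-36, ODI and RMDQ. Besides age, sex and K-classification, "models will be adjusted for other participant characteristics if differences are found from baseline to week 12". The variables given in brackets are the TSK score, the PCS score and daily steps.
- **Table 2.** The caption covers outcome measures and participant characteristics: "Collected weeks 0–1 (baseline) and 12–13 (post-intervention/wait-list controls"). PCS and TSK-11 are listed among the participant characteristics.
- **Discussion.** Less back pain from resistance exercise is expected to bring less catastrophizing and more steps per day.

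**The concern.** A variable measured after randomisation that responds to treatment, or to the pain relief treatment brings, is not a legitimate adjuster for the total treatment effect. Holding it constant removes whatever part of the effect runs through it, or is reflected in it, and gives up the protection of randomisation. The closing sentence of Participant characteristics makes change on study the very criterion for becoming a covariate and sets no limit on where it applies. Read literally, it reaches the primary comparison of pain between HBRX and CON.

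The trigger in Statistical analysis raises a second problem. Adjusters enter if they are found to have changed, so the aim 3 model depends on the results. The test, the threshold and whether change is judged overall or by arm are not given. The trigger also needs two measurements of TSK and PCS, and the document is not consistent on whether the second is taken.

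**Working it through.** **1. Where does the covariate rule apply?**

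| Section | Covariate | Scope given |
|---|---|---|
| Daily step count | Change in steps | Aim 3 |
| Participant characteristics, mid-paragraph | TSK, PCS | Aim 3 |
| Participant characteristics, last sentence | Any other variable that changes | None |
| Statistical analysis, aims 1 and 2 | None named beyond group and time | Open list |
| Statistical analysis, adjustment sentence | TSK, PCS, steps | Follows the aim 3 regression |

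One sentence lacks a limit that the others carry or take from their context. Nothing in the aims 1 and 2 description excludes it.

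**2. Is the rule for the aim 3 adjusters consistent?**

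- Step change: always a covariate in Daily step count; only if a change is found in Statistical analysis. Both cannot hold.
- TSK and PCS: measured at baseline in the text; at weeks 0–1 and 12–13 under the Table 2 caption. The trigger can be applied on the Table 2 schedule but not on a baseline-only one.

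**3. What could it do to the treatment effect if applied in aims 1 and 2?**

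The plan's own figure is 80% power with 16 per group at α = 0.05. No effect size, SD or sidedness is stated, so it cannot be reproduced forwards. Working backwards, assuming a two-sided test:

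d = (1.96 + 0.84) × √(2/16) = 2.80 × 0.354 = 0.99 (normal approximation); 1.02 with the t distribution.

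Take d = 1.02 as the total effect in SD units, signed so that benefit is positive. All values of a, b and r below are assumptions.

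*Model A: the covariate M lies on the pathway to pain.* Group shifts M by a SD, and pain change has within-group slope b on M. In a change-score model with M included, the group coefficient is d − ab. Simulation used 16 per group and 10,000 runs.

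| a | b | d − ab | Share removed | Simulated coefficient | Power |
|---|---|---|---|---|---|
| 0.5 | 0 | 1.02 | 0% | 1.02 | 76% |
| 1.0 | 0 | 1.02 | 0% | 1.02 | 69% |
| 0.5 | 0.3 | 0.87 | 15% | 0.87 | 67% |
| 1.0 | 0.5 | 0.52 | 49% | 0.53 | 32% |

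Unadjusted power in the same runs was about 80%. With b = 0 there is no bias, but precision is lost because M is correlated with group.

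*Model B: M responds to treatment only through pain, with within-arm correlation r.* The coefficient is d(1 − r²), here with d = 1.024:

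- r = 0.3: 1.024 × 0.91 = 0.93 (9% smaller)
- r = 0.5: 1.024 × 0.75 = 0.77 (25% smaller)
- r = 0.7: 1.024 × 0.51 = 0.52 (49% smaller)

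Simulated power was about 73–75%, 63% and 45–46%.

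*Model C: M enters the planned mixed model as one value per participant, as a main effect only.* With complete data at both times, its contribution γM is the same at baseline and week 12:

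(Y₁₂ − γM) − (Y₀ − γM) = Y₁₂ − Y₀.

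The group-by-time contrast is unchanged, so there is no shrinkage. Shrinkage needs a change-score model or, equivalently, an interaction of M with time; a time-varying covariate could also shift the estimate.

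The consequence therefore runs from none to about half the effect, depending on choices the document does not make.

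**The case against.** The strongest reply is that the document describes no treatment-effect model containing these covariates. Steps, TSK and PCS are each tied to aim 3, the unrestricted sentence ends a paragraph about the aim 3 model, and the aims 1 and 2 model names only group and time. Aim 3 relates change in pain to other changes by design and lists no group term, so it has no HBRX–CON difference to adjust away. This stands. A reader might infer that the primary comparison will be biased towards zero; the text permits that analysis but does not plan it. The reply does not rescue the sentence itself, which is a positive statement about the analyses in general.

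A reader might also infer that the TSK and PCS rule cannot be run. That is too strong. The text says these scales are measured at baseline, not that this is the only time, and the Table 2 caption gives both visits. What remains is an inconsistency.

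Third, the trigger might be read as picking exactly the variables treatment moved. It looks at change over time, not at a difference between arms, so a trend common to both arms would also set it off. It is still driven by the data.

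Finally, the percentages above might be read as the loss to expect here. They rest on assumed correlations, a back-solved effect size and, where there is shrinkage, a change-score model that the protocol does not specify. They show only that the loss could matter.

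**Conclusion.** The point holds as a defect of wording with a possible consequence for the primary analysis. Three things are established from the text alone:

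- a post-randomisation covariate rule with no limit to aim 3;
- a results-dependent trigger for the TSK, PCS and step adjusters, which contradicts the unconditional use of step change;
- conflicting statements on when TSK-11 and PCS are collected.

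That following the first rule in aims 1 and 2 could bias the comparison, usually towards zero, rests on the Discussion's own expectation that steps and catastrophizing respond to the intervention. No single figure for the bias can be given. The second and third defects affect the aim 3 model however the first sentence is read.

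**What to change.** 1. In Participant characteristics, delete the closing sentence or limit it explicitly to aim 3.
2. In Statistical analysis, state that the aims 1 and 2 models adjust only for baseline covariates named in advance, and never for a variable measured after randomisation.
3. Replace the change-based trigger with an aim 3 covariate list fixed before the data are examined. Give one rule for step change and use it in both Daily step count and Statistical analysis.
4. Reconcile the Participant characteristics text with Table 2 and Statistical analysis on whether TSK-11 and PCS are collected at baseline only or also at weeks 12–13, and say which values enter the aim 3 model.

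The cost is analysis wording only. If the scales are in fact taken at baseline only, the Table 2 caption needs an exception for them; if they are taken twice, the text needs the second visit added.
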